### *3.2 Secondary outcome*

The secondary outcome is self-reported number of opioid tablets used following surgery.

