### *8.2 Procedures*

After providing informed consent, participants will be sent messaging on post-operative days 4, 7, 14, 21, and 28. At each time point, patients are asked to self-report pain intensity (scale 0-10, 10 being severe), ability to manage pain (scale 0-10, 10 being very able to manage), and use of non-opioid and opioid analgesics. Patients who are using opioid analgesics are asked to report quantity used, projection of future use for acute pain. Patients reporting no further use are asked about disposal (Yes or No).

Patients will be mailed opioid disposal packets, DispoRx, which are small chemical polymers which individuals can pour directly into a pill bottle. The individual shakes the bottle and the medication is deactivated, rendered unusable and can be placed safely in the trash. We will mail these packets to individuals within the first 7 days for Orthopedic and Urology and timed for 21 days for Neurosurgery.

145 Participants will be randomly assigned at the individual level to receive a disposal packet. Participants  
146 randomized to the control arm will receive no other interventions.

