## 147 **9. Analysis plan**

148 To compare sample characteristics between arms we will use t-tests or Wilcoxon rank-sum tests (F-tests or  
149 Kruskal-Wallis test) for continuous variables and Pearson chi square tests or Fisher's exact tests for categorical  
150 variables. In our primary analyses, we will compare rates of opioid disposal (baseline vs. 6-week study period).  
151 In the secondary analysis we will compare self-reported pain intensity, ability to manage pain, and opioid use.  
152 All hypothesis tests will be two-sided using a two-sided alpha of 0.025 as our threshold for statistical  
153 significance. We will use Stata and/or SAS to analyze the data.

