**Q4:**

*"We just have a few more questions. [line break] Have you taken any of the following medications for your pain since your procedure (Acetaminophen, Aspirin, Ibuprofen, or Naproxen)? [Y for yes or N for no]. "*

326 LOGIC:

327 ○ If response = Y, N, yes, or no → Proceed to **Q5**

328 ○ If response ≠ Y, N, yes or no → REPLY "I'm sorry. We don't understand. Please text back Y or N."

329

330 **Q5:**

331 *"Thanks, this information helps guide our practice. It looks like you were also prescribed [opioid\_RX] for your*

332 *pain. [line break]Have you taken this medication? [Y for yes or N for no]."*

333

334 LOGIC:

335 ○ If response = Y or yes → Proceed to **Q6**

336 ○ If response = N or no → Proceed to **Q10**

337 ○ If response ≠ Y, N, yes or no → REPLY "I'm sorry. We don't understand. Please text back Y or N."

338

339 **Q6:**

340 *"Can you estimate how many pills of [opioid\_RX] you have taken since your procedure? Please text back a*

341 *number"*

342 LOGIC:

343 ○ If response = Number → Proceed to **Q7**

344 ○ If response ≠ Number → REPLY "I'm sorry. We don't understand. Please text back a number."

345

346

347 **Q7:** *"Do you have any of these pills remaining? [Y/N]"*

348 LOGIC:

349 ○ If response = Y, yes → Proceed to **Q8**

350 ○ If response = N, no Proceed to **Q10**

351 ○ If response ≠ Y, N, yes or no → REPLY: *"I'm sorry. We don't understand. Please text back Y or N."*

352

353

354 **Q8:** *"Do you plan to continue taking [opioid\_RX] to control your pain? [Y/N]"*

355 LOGIC:

356 ○ If response = Y or yes → REPLY: *"Thanks so much for your feedback! We'll check back with you in a few*

357 *days. If you have any questions or concerns about your care or health please contact your surgical team.*

358 *Have a nice day!"*

359

360 ---This patient will be texted in 1 week---

361

362  
363  
364  
365  
366  
367  
368  
369  
370  
371  
372  
373  
374  
375  
376  
377  
378  
379  
380  
381  
382  
383  
384  
385

- If response = N or no → **Move to Q9**
- If response ≠ Y, N, yes or no → REPLY: *"I'm sorry. We don't understand. Please text back Y or N."*

**Q9:** "Have you disposed of your unused %opioid% medication? [Y/N]"

LOGIC:

- If response = Y or Yes → That's great to hear. It's important to dispose of your unused medication. Just one more question for you: [line break] *"How many days did it take for your pain to improve after your procedure? Please text back a number."*

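### Section 8.2 asks everyone about pain through day 28, but the text script states re-contact only for people continuing opioids, so the later-day pain comparison is open to selection

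*Supplement*

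**What the plan says.** **Analysis plan (section 9).** "In the secondary analysis we will compare self-reported pain intensity, ability to manage pain, and opioid use". No day, population or missing-data rule is given. Section 3.2 does not list pain: "The secondary outcome is self-reported number of opioid tablets used following surgery". Pain therefore enters as a between-arm comparison through section 9 alone.

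**Procedures (section 8.2).** After consent, "participants will be sent messaging on post-operative days 4, 7, 14, 21, and 28". On content: "At each time point, patients are asked to self-report pain intensity (scale 0-10, 10 being severe), ability to manage pain". No stopping condition is attached.

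**Text-message script (end of the protocol).** Items Q2 and Q3 ask about pain and managing it, and items Q5 to Q9 ask about the opioid. A further contact is stated only after a yes at item Q8 (plans to continue): "This patient will be texted in 1 week". For someone who never took the opioid, item Q5 says "If response = N or no → Proceed to Q10", the closing question. Someone who reports disposal at item Q9 is told "That's great to hear. It's important to dispose of your unused medication" and then gets one last question.

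**Context.** Section 8.1 says neither the questions nor their timing will be altered. Under section 5.1 the kit is mailed only after the participant responds and consents on day 4. Section 8.2 puts mailing within the first 7 days for orthopedics and urology, and at about 21 days for neurosurgery.

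**The concern.** The two descriptions yield different data sets. Under section 8.2, each arm has pain scores on every scheduled day from everyone who answers. Under the script's stated contacts, a participant leaves the pain series on reporting that the opioid was not taken, has run out or is no longer planned.

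That exit happens after assignment, and the kit could influence it. Comparing arms among those still being texted would then condition on a consequence of treatment. If people with less pain stop sooner, and the kit brings stopping forward, mean pain among those still asked rises in the kit arm with no true effect on pain. The opposite selection could hide a real worsening. In either case, pain after the exit session is missing, so the plan could not show how people fare once they have left.

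**Working it through.** No figure in the plan bears on this point. The one design figure, power for the disposal comparison, is unaffected: 125 per arm, 25% versus 45%, two-sided alpha 0.025 gives 86%, consistent with the stated minimum of 80%.

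**Step 1. Trace the routes through the script.**

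| Answer | Next step | Re-contact stated? |
|---|---|---|
| Q5 no (opioid not taken) | Q10, closing question | No |
| Q7 no (no pills left) | Q10, closing question | No |
| Q8 yes (will continue) | Reply promising another check-in | Yes, in one week |
| Q8 no, Q9 yes (disposed) | Praise, closing question | No |
| Q8 no, Q9 no (not disposed) | Take-back information, closing question | No |

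The closing question asks, in the past tense, how long pain took to improve. The reply after Q10 omits the promise of another check-in that the Q8 yes reply contains.

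**Step 2. Who supplies pain scores if the script governs?**
- Day 4: all responders, before any kit is mailed.
- Later days: those who answered yes at Q8 at the previous contact. Q2 and Q3 come before Q5 to Q9, so a person who stops is still scored in the session where stopping is reported.
- After that session: nothing.

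Q9 yes and Q9 no have the same stated follow-up. Exit therefore turns on Q5, Q7 and Q8, that is, on stopping and not on disposal itself.

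**Step 3. When would this bias the comparison?** Two conditions are needed: the kit changes stopping, and stopping relates to pain. The documents establish neither.

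**Step 4. Illustrations. Every input is assumed; none comes from the documents.**

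*Extreme case.* Remove exactly the lowest fraction q of a normal distribution. The mean of the remainder rises by φ(z_q)/(1−q) SD.
- q = 0.10: 0.1755/0.90 = 0.195 SD. With SD 2, that is 0.39 points.
- q = 0.20: 0.2800/0.80 = 0.350 SD. With SD 2, that is 0.70 points.

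This is the largest upward shift possible for a given fraction removed, so it is an upper limit and not an expectation.

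*Simulation, 400,000 per arm.* Mean pain is 5.0, 4.2, 3.2, 2.6 and 2.2 on days 4, 7, 14, 21 and 28. The SD is 1.8 between people and 1.2 within, with scores held to 0–10. The log-odds of stopping at a contact are −0.6 − 0.5 × (pain − day mean). The kit adds a constant from day 7 and has no true effect on pain.

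| Log-odds added by kit | Still asked at day 28, control / kit | Observed difference, day 28 | Difference if all were asked |
|---|---|---|---|
| 0 | 21.4% / 21.3% | 0.02 | 0.01 |
| 0.5 | 21.5% / 14.6% | 0.26 | 0.00 |
| 1.0 | 21.4% / 9.0% | 0.52 | 0.00 |

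The first row is simulation noise around zero. With 125 responders per arm, the last row would leave about 125 × 0.214 = 27 control and 125 × 0.090 = 11 kit participants. If stopping is also assumed to raise later pain by 1 point, the last row's observed difference is 0.53 while the difference among everyone becomes 0.12. The restricted comparison barely responds to the effect of interest.

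**The case against.** The strongest reply is that nothing in the documents says messaging ends. Section 8.2 gives the schedule without conditions, and the opening of item Q2 leaves further contacts open. The Q8 note is loose: it says one week, the reply beside it says a few days, and day 4 to day 7 is three days. The opening script item is not visible in the copy reviewed, and other text was removed, so a re-contact rule may stand there. This holds. A reader might infer that the script definitely stops; that is an inference from the single re-contact note, the closing question and the closing reply. What is established is an unreconciled conflict. Section 8.1 does not settle it, because it fixes the timing without saying which description is the existing timing.

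Three other stronger readings also fail:
- *Pain after disposal is never measured.* Someone who disposed between two contacts gives one post-disposal score in the session that reports it. What would be lost is pain after that session.
- *The later comparison is biased.* A kit that raises disposal only among people who have already stopped leaves the texted group unchanged. Open to bias is as far as the documents go.
- *Uncontrolled pain is the foreseeable harm.* Section 11.6.1 anticipates only a breach of confidentiality, and disposal is asked only of people who report no further planned use. The point does not need this premise.

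**Conclusion.** The concern holds as a conflict between section 8.2 and the script, with a consequence for the pain comparison in section 9. It rests on one assumption: that the script, run unchanged, re-contacts only those for whom it states re-contact. Under it, the only contact shared by all responders precedes the kit, later scores come from people who planned at their previous contact to continue opioids, and pain after the exit session is missing.

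The size of any bias cannot be derived from the documents. It is about zero if exit is equal by arm. The 0.26 and 0.52 points, and the 0.39 and 0.70 points, show direction and plausibility under assumed inputs only and should not be read as predictions for this trial. If section 8.2 is what will run, this selection does not arise, and only the missing days, population and missing-data rule in section 9 remain. The point concerns a secondary comparison and does not change the stated sample size or power.

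**What to change.** 1. Reconcile section 8.2, the script and the section 8.1 statement on unchanged timing. State in the script that items Q2 and Q3 go to every consenting participant in both arms on days 4, 7, 14, 21 and 28, whatever was answered at Q5 to Q9.
2. In section 9, name the post-kit days for the pain comparison, allowing for the different mailing times by specialty. Make it among all assigned participants, and state a missing-data rule. Non-response will remain even with full messaging, so report response by arm and day.
3. Align section 3.2 with section 9 on whether pain is a secondary outcome.
4. If people who have stopped cannot be re-texted, state that the trial cannot give an unselected between-arm comparison of pain after the kit. Do not substitute the day-4 comparison, which precedes the kit.

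Cost: two automated questions per scheduled day, which section 8.2 already promises, and slightly more texting for people who have stopped opioids. If existing practice does end contact early, message timing changes, and section 8.1, with any approval that relies on it, must be updated. If existing practice already follows section 8.2, one clarifying sentence in the script settles the messaging part.

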## 159 **11. Human research protection**

### 160 *11.1 Data confidentiality*

161 The study will utilize a client-server deployed Data Management System (DMS) rather than a 'Store and  
162 Forward' database configuration, obviating research site database security concerns. Confidential participant  
163 information will be entered into the database. If this information exists on paper CRFs, it will be filed under lock  
164 and key, with generation of a participant ID. Thereafter, confidential information will be made available to  
165 authorized users only as specifically needed. No one can gain access to an individual MySQL database table  
166 unless explicitly granted a user ID, password, and specific access. Even those with user names and  
167 passwords cannot gain access to the tables that contain the identifying participant information.

168 No results will be reported in a personally identifiable manner. All tracking system data will be password-  
169 protected with several levels of protection. The first will allow access to the operating system of the computer.  
170 The second will allow access to the basic menus of the integrated system; within certain menu options, such  
171 as database browsing, a third password will be required. Our prior research employing similar precautions has  
172 demonstrated that these techniques are very successful in assuring the protection of subjects.

173 Each investigator and staff member involved in the proposed study will sign and adhere to a Standard  
174 Operating Procedure for managing participant data through the automated texting platform and has  
175 participated in required IRB/HIPAA compliance training. We will also continue to make use of password  
176 protection programs for all computerized records. In no instances will identifying information be publicly  
177 disclosed. Prior to conducting any analyses, all identifiers (e.g., names, medical record numbers, health plan  
178 enrollee numbers, birth dates, etc. will be removed. Results from this part of the investigation will be reported in  
179 aggregate. All participant identification will be removed from the data 3 years after the study has been  
180 completed.

### 181 *11.2 Subject confidentiality*

All participants will provide informed consent for access to these materials. The data to be collected include demographic data (e.g., age, sex, self-identified race), prescription data, self-reported pain, use and disposal. Research material that is obtained will be used for research purposes only. The same procedure used for the analysis of automated data sources to ensure protection of patient information will be used for the survey data, in that patient identifiers will be used only for linkage purposes or to contact patients. The study identification number, and not other identifying information, will be used on all data collection instruments. All study staff will be reminded to appreciate the confidential nature of the data collected and contained in these databases. The Penn Medicine Academic Computing Services (PMACS) will be the hub for the hardware and database infrastructure that will support the project and is where the Way to Health web portal is based. The PMACS is a joint effort of the University of Pennsylvania's Abramson Cancer Center, the Cardiovascular Institute, the Department of Pathology, and the Leonard Davis Institute. The PMACS provides a secure computing environment for a large volume of highly sensitive data, including clinical, genetic, socioeconomic, and financial information. Among the IT projects currently managed by PMACS are: (1) the capture and organization of complex, longitudinal clinical data via web and clinical applications portals from cancer patients enrolled in clinical trials; (2) the integration of genetic array databases and clinical data obtained from patients with cardiovascular disease; (3) computational biology and cytometry database management and analyses; (4) economic and health policy research using Medicare claims from over 40 million Medicare beneficiaries. PMACS requires all users of data or applications on PMACS servers to complete a PMACS-hosted cybersecurity awareness course annually, which stresses federal data security policies under data use agreements with the university. The curriculum includes Health Insurance Portability and Accountability Act (HIPAA) training and covers secure data transfer, passwords, computer security habits and knowledge of what constitutes misuse or inappropriate use of the server. We will implement multiple, redundant protective measures to guarantee the privacy and security of the participant data. All investigators and research staff with direct access to the identifiable data will be required to undergo annual responsible conduct of research, cybersecurity, and HIPAA certification in accordance with University of Pennsylvania regulations. All data for this project will be stored on the secure/firewalled servers of the PMACS Data Center, in data files that will be protected by multiple password layers. These data servers are maintained in a guarded facility behind several locked doors, with very limited physical access rights. They are also cyber-protected by extensive firewalls and multiple layers of communication encryption. Electronic access rights are carefully controlled by University of Pennsylvania system managers. We will use highly secure methods of data encryption for all transactions involving participants' financial information using a level of security comparable to what is used in commercial financial transactions. We believe this multi-layer system of data security, identical to the system protecting the University of Pennsylvania Health Systems medical records, greatly minimizes the risk of loss of privacy. In addition, risk of loss of confidentiality will be minimized by storing completed paper copies of the surveys and signed informed consent forms in locked file cabinets in locked offices accessible only to trained study staff. Each subject will be assigned a unique identifier without identifying information, and data will be entered into an electronic database using only the unique identifier. Only trained study staff will have access to the code that links the unique identifier to the subject's identity. Electronic data will be stored on secure, password-protected firewalled servers at the University of Pennsylvania.

### *11.3 Subject privacy*

Interested participants will provide consent via text messaging. Enrollment will include a description of the voluntary nature of participation, the study procedures, risks and potential benefits in detail.. Participants will be

224 told that they do not have to answer any questions if they do not wish and can drop out of the study at any time,  
225 without affecting their medical care or the cost of their care. They will be told that they may or may not benefit  
226 directly from the study and that all information will be kept strictly confidential, except as required by law.

#### 227 *11.4 Data disclosure*

228 No other entities will have access to this data.

#### 229 *11.5 Data safety and monitoring*

230 The automated texting system staff is responsible for preventing unauthorized access to the trial participant  
231 tracking system database through its use of secure network firewall technologies. The study will utilize a client-  
232 server deployed Data Management System (DMS) rather than a 'Store and Forward' database configuration,  
233 obviating research site database security concerns. Confidential participant information will be entered into the  
234 database. If this information exists on paper CRFs, it will be filed under lock and key, with generation of a  
235 participant ID. Thereafter, confidential information will be made available to authorized users only as  
236 specifically needed. No one can gain access to an individual MySQL database table unless explicitly granted a  
237 user ID, password, and specific access. Even those with user names and passwords cannot gain access to the  
238 tables that contain the identifying participant information.

239 No results will be reported in a personally identifiable manner. All tracking system data will be password-  
240 protected with several levels of protection. The first will allow access to the operating system of the computer.  
241 The second will allow access to the basic menus of the integrated system; within certain menu options, such  
242 as database browsing, a third password will be required. Our prior research employing similar precautions has  
243 demonstrated that these techniques are very successful in assuring the protection of subjects.

244 Each investigator and staff member involved in the proposed study will sign and adhere to a Standard  
245 Operating Procedure for managing participant data through the automated texting platform and has  
246 participated in required IRB/HIPAA compliance training. We will also continue to make use of password  
247 protection programs for all computerized records. In no instances will identifying information be publicly  
248 disclosed. Prior to conducting any analyses, all identifiers (e.g., names, medical record numbers, health plan  
249 enrollee numbers, birth dates, etc.) will be removed. Results from this part of the investigation will be reported  
250 in aggregate. All participant identification will be removed from the data 3 years after the study has been  
251 completed.

#### 252 *11.6 Risk/benefit*

##### 253 *11.6.1 Potential study risks*

254 The anticipated potential risks for participants who are enrolled in this study are (1) harm resulting from a  
255 breach of confidentiality.

256 Harm resulting from a breach of confidentiality for all participants could include persons getting inappropriate  
257 access to interview/clinical data. Participants are at risk to be identified as someone who reports using opioids  
258 to manage pain.

259 Data collected in the study will be kept strictly confidential and will not be shared with anyone outside of the  
260 research team. The only exceptions to confidentiality, which will be clearly specified in the consent form, will be  
261 for information related to medical emergencies, current child abuse or neglect, or imminent risk of death or  
262 serious injury to the participant or others.

All project staff will be required to undergo training in confidentiality procedures (including HIPAA regulations) which review data handling procedures, as well as addressing questions about participants posed by individuals outside of the immediate project staff and by project staff members who do not need the information requested. Certification of successful completion of this training is kept in the appropriate project binder. Should any breaches of participant confidentiality occur during the course of the study, they will be reported to the relevant IRB, DSMB and NIDA officials.

